### Randomization and blinding

2.6

This is a single-center study conducted at Hangzhou Hospital of TCM. Randomization will be performed by an independent statistician who is not involved in patient recruitment, intervention, or outcome assessment. The randomization sequence will be generated using SAS software version 9.4, with a 1:1 allocation ratio, stratified by sex, and age, utilizing random block sizes of six. Allocation concealment will be ensured using a centralized system, and researchers, participants, and data administrators and statisticians will be unaware of the randomization and treatment allocations. To ensure the blinding of participants and investigators, the placebo is identical to FJHQG in appearance, color, taste, packaging. Emergency unblinding will only be performed when necessary for patient safety and must be approved by principal investigator, and all such events will be documented.

### Intervention

2.7

Every participant will be treated following the “2018 Chinese Guidelines for Heart Failure Diagnosis and Management” (15). This therapeutic plan involves diuretics, angiotensin-converting enzyme inhibitor (ACEI), angiotensin receptor blocker (ARB), angiotensin receptor-neprilysin inhibitor (ARNI), beta-blockers, and other suggested treatments. Optimal medical management will be ensured in alignment with the guidelines. All background medication will follow guideline-directed medical therapy. All concomitant medications and treatment adjustments during the study will be recorded in detail, and potential between-group differences will be summarized and adjusted. In addition, the intervention group will be given FJHQG, while the control group will undergo conventional drug therapy and corresponding placebo, both for a duration of 12 weeks. FJHQG is manufactured by CHIATAI QINGCHUNBAO PHARMACEUTICAL Co., Ltd. in accordance with Good Manufacturing Practice standards. All study medications will be provided by the manufacturer in standardized packaging. To ensure traceability, batch numbers will also be recorded (batch number: 2308702). The placebo will be identical to FJHQG in appearance, taste, and packaging to maintain blinding. Participants will be instructed to consume the granules (5 g per dose, twice daily). To guarantee adherence, the granules will be handed out and/or gathered during every visit. Adherence will be assessed based on sachet counts and patient-reported intake and will be calculated as the proportion of sachets taken relative to the total number prescribed. Missed doses and treatment interruptions will be recorded, and adherence below 80% will be considered a protocol deviation. During the trial, the use of other traditional Chinese medicine that may affect diuretic function is strictly prohibited.

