HF is often treated with Traditional Chinese Medicine (TCM) because of proven efficacy in ameliorating symptoms. According to TCM theory, HF mainly arises from a deficiency of heart Qi and blood stagnation. This condition denotes a pathological state wherein Qi is unable to facilitate effective blood circulation, leading to impaired or stagnant blood flow. Clinically, heart Qi deficiency usually manifests as fatigue, shortness of breath, palpitations, and impaired exercise tolerance, reflecting insufficient cardiac driving force. Blood stasis is associated with chest tightness or pain, and cyanosis of the lips, indicating impaired blood circulation. Water stasis results from an inability of Qi deficiency and blood stasis to regulate fluid metabolism and is typically manifested by peripheral edema, orthopnea, abdominal distension, and reduced urine output, which are typical symptoms of HF. The FangJi HuangQi (FJHQ) decoction, a renowned prescription in TCM comprises the following Chinese medicinal ingredients: *Astragalus membranaceus* (Fisch.) Bge. (6 g), *Stephania tetrandra* S. Moore (1.5 g), *Atractylodes macrocephala* Koidz*.* (3 g), *Glycyrrhiza uralensis* Fisch. (1 g), *Lepidium apetalum* Willd. (2.5 g), *Prunella vulgaris* L. (3 g), and *Salvia miltiorrhiza* Bunge (4 g). This formulation is reputed for its ability to “reinforce qi and improve blood circulation, invigorate spleen function, and clear water”. Extensive preliminary research has demonstrated that the herbs in the FJHQ decoction are both safe and effective (3, 4). Moreover, toxicological evaluations in rats revealed no noticeable negative impacts on the central nervous, respiratory, or cardiovascular systems, thus confirming the compound's safety (5, 6). In rats with pulmonary artery hypertension, the FJHQ decoction improved hemodynamic parameters, enhanced lung function, and lessened pulmonary vascular remodeling (7). In addition, FJHQ decoction has shown its effects in several cardiovascular conditions including hypertension, myocardial ischemia, and cardiac fibrosis (8). It has been shown that FJHQ decoction effectively improved exercise capacity and reduced diuretic usage and resistance without significant liver or kidney damage or adverse events in small-scale clinical observations (9, 10). However, there is still a lack of clinical evidence regarding the effectiveness and safety of FJHQ decoction in patients with HF.

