### Inclusion criteria

2.3

The study will include participants who satisfy all of the following inclusion criteria:
Diagnosis of chronic heart failure in a stable condition (defined as no acute decompensation, and no hospitalization for heart failure within at least 2 weeks before randomization), classified as heart failure with mildly reduced ejection fraction (LVEF: 41%–49%) or heart failure with preserved ejection fraction (LVEF≥50%), with BNP ≥35 pg/mL, and at least one of the following echocardiographic features present: left ventricular hypertrophy and/or left atrial enlargement; diastolic dysfunction, according to the 2018 Chinese Guidelines for the Diagnosis and Treatment of Heart Failure, and meeting the criteria of “Qi deficiency, blood stasis, and water stasis” syndrome;Patients must be on stable guideline-directed medical therapy for heart failure prior to randomization, defined as no major changes in medications within at least 2 weeks;NYHA classification of II to III;Age between 18 and 80 years;Voluntary acceptance the medication treatment and provision of an informed consent form trained investigators.

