### Follow-up visits and monitoring schedule

2.8

The study will start with a 7-day preliminary phase where eligible individuals will provide their consent and initial information will be gathered. Future appointments will be planned for 6 days ± 1 day (visit 1), 4 weeks ± 3 days (visit 2), and 12 weeks ± 3 days (visit 3) after starting the treatment. Follow-up assessments will be conducted at Week 12 ± 7 days post-discontinuation of treatment (24W ± 7d) (visit 4). To minimize loss to follow-up, participants will be regularly contacted through telephone calls and WeChat group communication. Reminders will be provided before each scheduled visit to improve retention and adherence. Table 1 outlines the comprehensive assessment timetable.

**Table 1 T1:** Schedule of enrollment, interventions, and assessments.

Study phase time	Lead-in period	Treatment period			Follow-up period
	Screening (−7D-0D)	Baseline (6D ± 1d)	Week 4 (4W ± 3d)	Week 12 (12W ± 3d)	Week 24 (24W ± 7D)^a^
Patients					
Eligibility screen	X				
Inclusion/exclusion criteria	X				
Informed consent	X				
General information	X				
Medical history	X				
Allocation	X				
Pregnancy examination	X				
Outcomes					
Primary outcome					
6-minute walk test	X	X	X	X	X^c^
Secondary outcomes					
BNP	X	X	X	X	X
MACE (including cardiac death, non-fatal myocardial infarction, and rehospitalization due to heart failure) ^b^	X	X	X	X	X
NYHA classification	X	X	X	X	X
KCCQ quality of life score	X	X	X	X	X
Exploratory outcomes					
Diuretic usage		X	X	X	X
Echocardiography	X			X	X
Heart failure-related rehospitalization rate^b^	X	X	X	X	X
TCM syndrome score	X	X	X	X	X
Myocardial enzyme levels	X			X	X
Inflammatory markers and other biochemical indicators	X			X	X
Safety					
Vital signs	X	X	X	X	X
Biochemical indexes	X			X	X
Electrocardiogram results	X			X	X
Adverse events	X	X	X	X	X
Others					
Drug distribution	X		X		
Drug recycle			X	X	
Combined medication			X	X	
Confirmation of medication compliance		X	X	X	X

a Visit 4 corresponds to the follow-up assessment conducted at Week 24, which is 12 weeks after completion of the 12-week treatment period, as stated in manuscript.

b Continuous monitoring throughout the study.

c Primary endpoint assessed at week 24.

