Other exploratory outcomes will include: (1) clinical outcomes including diuretic dosage, and 24-hour fluid intake and output (recorded for inpatients only); (2) TCM syndrome scale scoring; (3) cardiac structure outcomes including left ventricular ejection fraction, diastolic diameter, interventricular septal thickness, and posterior wall thickness indicated by echocardiography. Image acquisition and measurements will follow predefined procedures, and all echocardiographic data will be interpreted by experienced cardiologists who are blinded to treatment allocation to minimize assessment bias; (4) biochemical measurement outcomes including lipid profile (including total cholesterol, triglycerides, high-density lipoprotein cholesterol, low-density lipoprotein cholesterol, apolipoprotein A1, apolipoprotein B, and homocysteine), myocardial enzymes [including lactic dehydrogenase, creatine kinase (CK), and CK-MB], inflammation indicators [including C-reactive protein (CRP) and interleukin-6 (IL-6)] and other biochemical parameters (including bioactive adrenomedullin, CD146, vasopressin 2 receptor, cyclic adenosine monophosphate, protein kinase A, aquaporin 2, mucin 16, stromelysin 2, and soluble stromelysin 2). Specifically, bioactive adrenomedullin and CD146 are associated with endothelial function and vascular integrity, reflecting microcirculatory dysfunction. Vasopressin 2 receptor and aquaporin 2 are involved in water metabolism and fluid retention, representing fluid imbalance. Cyclic adenosine monophosphate and protein kinase A are key components of intracellular signaling pathways related to neurohormonal activation. In addition, stromelysin 2, soluble stromelysin 2, and mucin 16 are associated with extracellular matrix remodeling, inflammation, and tissue injury. Together, these biomarkers provide a comprehensive evaluation of endothelial dysfunction, fluid regulation, and neurohormonal activation, which are closely related to heart failure progression and may potentially reveal the mechanism of FJHQG in treatment of HF. Blood plasma will be gathered and kept at −80 °C in the lab freezer for analysis. Exploratory outcomes will be interpreted descriptively and will not be used for confirmatory inference.

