### Statistical analysis

2.15

All statistical analyses will be conducted on both the intention-to-treat (ITT) and per-protocol (PP) populations. The ITT population will include all randomized participants, while the PP population will consist of participants with at least 80% adherence to the protocol. Continuous variables following a normal distribution will be presented as means ± standard deviations (SD) with 95% confidence intervals (CI), and non-normally distributed variables will be reported as medians with interquartile ranges (IQR) and analyzed using non-parametric methods. Between-group comparisons for normally distributed continuous variables will use the independent samples t-test, and for non-normal distributions, the Wilcoxon rank-sum test. Within-group comparisons will employ paired t-tests or Wilcoxon signed-rank tests as appropriate. Categorical variables will be summarized as counts and percentages, with between-group comparisons using the Chi-square or Fisher's exact test, and within-group comparisons using the McNemar test. Baseline characteristics will be reported descriptively without significance testing to assess comparability between groups. Differences in background treatment between groups will be summarized descriptively and adjusted for in the statistical analysis to reduce potential confounding.

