The primary outcome (6-minute walk test) will be analyzed using analysis of covariance (ANCOVA) with baseline values and key covariates (age, sex) as covariates to adjust for potential confounding. Secondary outcomes, due to their diverse nature, will be analyzed using appropriate methods: continuous variables with t-test or Wilcoxon test, categorical variables with Chi-square or Fisher's exact test, and repeated measures or longitudinal data using linear mixed-effects models. To control for multiple comparisons among secondary outcomes, the false discovery rate (FDR) adjustment using the Benjamini-Hochberg method will be applied, and a hierarchical structure will be applied with the primary outcome taking precedence over secondary and exploratory outcomes. The primary analysis will be conducted according to the intention-to-treat (ITT) principle, including all randomized participants. If the proportion of missing 6MWT data is 5% or greater, missing data for the 6MWT will be handled using multiple imputation under the missing-at-random assumption. The imputation model will include baseline 6MWT value, age, sex, and treatment group as predictors. Imputation will be performed using a single model based on all available data without separating treatment arm. In addition, reasons for missing data will also be recorded, categorized, and summarized descriptively, and will be compared between groups. Prespecified subgroup analyses will be conducted based on heart failure phenotype, defined by left ventricular ejection fraction (LVEF ≥50% vs. <50%), and by sex. These subgroup analyses will be considered exploratory. Sensitivity analyses will be performed, including per-protocol analyses and complete-case analyses, to assess the robustness of the results. Deaths occurring before the final assessment will be handled in sensitivity analyses using a worst-case approach by assigning a value of zero for the 6MWT, representing the worst functional outcome. Adverse events will be summarized in tables and compared between groups using descriptive statistics. All analyses will be performed using SAS software version 9.4, and two-tailed *P*-values < 0.05 will be considered statistically significant. A detailed statistical analysis plan will be finalized prior to database lock to ensure prespecified analysis procedures.

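### Section 2.7 commits to adjusting for medication changes made after randomisation, which FJHQG may itself cause, and this conflicts with the covariates fixed for the primary ANCOVA in section 2.15

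*Protocol article*

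**What the plan says.** **Section 2.7 (Intervention)**, on treatment given during the trial: "All concomitant medications and treatment adjustments during the study will be recorded in detail, and potential between-group differences will be summarized and adjusted".

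**Section 2.15 (Statistical analysis)**, directly after the sentence on describing baseline characteristics: "Differences in background treatment between groups will be summarized descriptively and adjusted for in the statistical analysis to reduce potential confounding". No drug class, time point or model is named.

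**Section 2.15, primary outcome**: the six-minute walk test (6MWT) is to be analysed by "analysis of covariance (ANCOVA) with baseline values and key covariates (age, sex) as covariates to adjust for potential confounding". No medication term appears in this model or in the imputation model.

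**Section 2.3 (Inclusion criteria)**: "Patients must be on stable guideline-directed medical therapy for heart failure prior to randomization", with no major change for at least two weeks.

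**Introduction and section 2.9 (Outcomes)**: the decoction is said to have "effectively improved exercise capacity and reduced diuretic usage and resistance", and the exploratory outcomes include "clinical outcomes including diuretic dosage". Section 2.7 lists diuretics as part of background therapy.

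**Section 2.8, Table 1**: the row "Combined medication" is marked at weeks 4 and 12 only. A separate row for diuretic use is marked at Visit 1 and at weeks 4, 12 and 24.

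**The concern.** Randomisation balances, in expectation, what patients bring to the trial. It does not balance what happens to them afterwards. If FJHQG relieves congestion, patients on it may need less diuretic. If placebo patients worsen, their background therapy may be stepped up. A difference between arms in on-study medication can therefore be an effect of the drug. It is not a confounder of the treatment comparison. Entering it as a covariate removes part of the effect the trial is meant to measure, or opens a spurious path through the severity of illness that drives both medication and walking distance.

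Two things are at stake. One is what the estimate means: an effect conditional on later medication is not the total effect of assignment to FJHQG. The other is which rule governs. An analysis plan faithful to 2.7 would carry a medication covariate, and one faithful to the primary-outcome text of 2.15 would not.

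**Working it through.** **1. The plan's own sample size.** Section 2.14 gives a difference of 50 m, SD 72 m, two-sided α of 0.05, 90% power and 10% dropout.

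- Normal approximation: n = 2 × (1.960 + 1.282)² × 72² / 50² ≈ 43.6, so 44 per arm. The t-test version gives 44.6, so 45.
- Dropout: 45 / 0.90 = 50 per arm, 100 in total.

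The stated figures reproduce. Power at 45 per arm is 90.9% by the normal approximation.

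**2. Is the variable post-randomisation?** Section 2.3 requires stable therapy before randomisation, and 2.7 speaks of adjustments made during the study. The changes meant in 2.7 therefore include changes after randomisation. The 2.15 sentence alone does not settle its timing.

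**3. Can the drug affect it?** The Introduction reports reduced diuretic use with the decoction, and 2.9 lists diuretic dosage as an outcome. The article thus treats it as something FJHQG may change.

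**4. What adjustment does to the estimate.** Let *a* be the drug's effect on the on-study medication in within-arm SDs, and ρ the within-arm correlation of that medication with 6MWT. In a linear model:

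adjusted effect = total effect − (72 × ρ) × *a*

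Neither *a* nor ρ is in the article. The values below are **assumptions**. A negative *a* means that the drug lowers diuretic use. A negative ρ means that patients on more diuretic walk less far.

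| *a* | ρ | 72 × ρ × *a* | Adjusted effect if the total is 50 m |
|---|---|---|---|
| −0.25 | −0.1 | 1.8 | 48.2 m |
| −0.5 | −0.3 | 10.8 | 39.2 m |
| −0.8 | −0.5 | 28.8 | 21.2 m |
| 0 | any | 0 | 50.0 m |

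A simulation of the middle row (45 per arm, 10,000 runs) gave 49.9 m unadjusted and 39.1 m adjusted, with power of about 73%. With a true total effect of zero and the same *a* and ρ, the adjusted estimate averaged −10.8 m and the test rejected in about 11% of runs instead of 5%. With *a* = 0 the estimate was 50.0 m, and under a zero effect the rejection rate was 5.1%.

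Over the assumed grid, a simple power formula runs from about 89% down to 36%. It ignores the correlation between treatment and covariate and is somewhat optimistic: it gives 77% for the middle row, against 73% simulated.

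The direction is not fixed either. With ρ = +0.3 and *a* = −0.5, the adjusted effect would be 50 + 10.8 = 60.8 m.

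**5. Which analysis would carry the adjustment?** Section 2.15 names ANCOVA for the primary outcome, and t, Wilcoxon, chi-square or Fisher tests and linear mixed models for the secondary ones. The simple tests cannot hold a covariate. That leaves the ANCOVA, whose covariates are already listed without medication, the mixed models, or an analysis that is not named. The article does not say which.

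**The case against.** The strongest reply is that the primary model is already written down and contains no medication term. A reader might infer from 2.7 that the primary estimate is biased or that its type I error is inflated. The article does not support that. It shows a conflict between sections, and the simulated error rate describes only what would follow if the adjustment entered the test and the assumed values held. This objection stands and limits the point.

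Second, the 2.15 sentence on background treatment follows the one on baseline characteristics. It can be read as adjustment for the regimen at entry, which is harmless if prespecified. That also stands, but the wording of 2.7 cannot be read that way.

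Third, a reader might infer that covariates will be picked according to the imbalances observed. No such selection rule is stated. Statisticians are to be blinded (2.6), and a detailed analysis plan is promised before database lock. The details may properly be left to that plan. The commitment in 2.7 to adjust for on-study changes is still in the protocol, and the plan would inherit it.

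Fourth, a reader might infer from Table 1 that medication before treatment and after week 12 goes unrecorded. That goes too far. Diuretic use has its own row through week 24. Medical history is marked at screening, and the stable-therapy criterion cannot be checked without knowing the regimen. What remains is that the concomitant-medication row is narrower than the text of 2.7.

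**Conclusion.** The point holds as a badly fixed rule and an internal conflict. Section 2.7 prescribes adjustment for on-study medication differences, and the confounding reason given in 2.15 does not justify it for differences that arise after randomisation. The article itself presents diuretic use as a possible drug effect and lists it as an outcome. Adjusting for it can bias the estimate of the total effect, and a larger sample would not remove that bias.

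Size and direction cannot be determined from the article. The range of 48 m to 21 m for a true 50 m rests wholly on assumed values of *a* and ρ, and the bias is nil if FJHQG does not change medication. Whether the primary estimate is affected is open, because the primary ANCOVA lists only baseline value, age and sex. The Table 1 mismatch is minor and is not evidence of bias.

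**What to change.** - **Section 2.7:** delete the words *and adjusted*, so that on-study medication is recorded and summarised by arm.
- **Section 2.15:** replace the background-treatment sentence with one that limits adjustment to covariates measured before randomisation and fixed in advance: baseline 6MWT, age, sex and, if wanted, class of background therapy at screening. If that class is added, list it in the ANCOVA sentence too, so that the two agree.
- **Section 2.15:** state that medication changes after randomisation are not covariates in the main comparison, which then estimates the effect of assignment whatever later treatment is given (a treatment-policy strategy).
- **Table 1 (minor, separate):** reconcile the concomitant-medication row with the recording promised in 2.7, noting that diuretic use is already scheduled from Visit 1 to week 24.

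The cost is two sentences, one clarifying line and a check of one table row. Any marks added to that row would mean a few more case report form entries at visits that already take place. The sample size does not change. The text should be settled before the analysis plan is finalised and the database locked.

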### Follow-up visits and monitoring schedule

2.8

The study will start with a 7-day preliminary phase where eligible individuals will provide their consent and initial information will be gathered. Future appointments will be planned for 6 days ± 1 day (visit 1), 4 weeks ± 3 days (visit 2), and 12 weeks ± 3 days (visit 3) after starting the treatment. Follow-up assessments will be conducted at Week 12 ± 7 days post-discontinuation of treatment (24W ± 7d) (visit 4). To minimize loss to follow-up, participants will be regularly contacted through telephone calls and WeChat group communication. Reminders will be provided before each scheduled visit to improve retention and adherence. Table 1 outlines the comprehensive assessment timetable.

**Table 1 T1:** Schedule of enrollment, interventions, and assessments.

Study phase time	Lead-in period	Treatment period			Follow-up period
	Screening (−7D-0D)	Baseline (6D ± 1d)	Week 4 (4W ± 3d)	Week 12 (12W ± 3d)	Week 24 (24W ± 7D)^a^
Patients					
Eligibility screen	X				
Inclusion/exclusion criteria	X				
Informed consent	X				
General information	X				
Medical history	X				
Allocation	X				
Pregnancy examination	X				
Outcomes					
Primary outcome					
6-minute walk test	X	X	X	X	X^c^
Secondary outcomes					
BNP	X	X	X	X	X
MACE (including cardiac death, non-fatal myocardial infarction, and rehospitalization due to heart failure) ^b^	X	X	X	X	X
NYHA classification	X	X	X	X	X
KCCQ quality of life score	X	X	X	X	X
Exploratory outcomes					
Diuretic usage		X	X	X	X
Echocardiography	X			X	X
Heart failure-related rehospitalization rate^b^	X	X	X	X	X
TCM syndrome score	X	X	X	X	X
Myocardial enzyme levels	X			X	X
Inflammatory markers and other biochemical indicators	X			X	X
Safety					
Vital signs	X	X	X	X	X
Biochemical indexes	X			X	X
Electrocardiogram results	X			X	X
Adverse events	X	X	X	X	X
Others					
Drug distribution	X		X		
Drug recycle			X	X	
Combined medication			X	X	
Confirmation of medication compliance		X	X	X	X

a Visit 4 corresponds to the follow-up assessment conducted at Week 24, which is 12 weeks after completion of the 12-week treatment period, as stated in manuscript.

b Continuous monitoring throughout the study.

c Primary endpoint assessed at week 24.

Basic details encompass full name, birthdate, sex, race, job status, and more. The patient's medical background encompasses a present diagnosis of HF and previous health records. Biochemical indicators encompass blood, urine, feces, and the functioning of the liver, kidneys, and coagulation system.

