### Outcomes

2.9

The primary outcome of the trial will be the variation in the 6-minute walk test by week 24 as compared to baseline. The assessment of 6MWT will be performed in accordance with standardized procedures. The test will be conducted in a 30-meter corridor, and standardized instructions and encouragement will be provided to all participants. To ensure patient safety and consistency, predefined stopping criteria including intolerable dyspnea, chest pain, dizziness, or any other symptoms indicating potential risk, as judged by the assessor, will also be applied. The use of walking aids or supplemental oxygen will be permitted if clinically necessary, and the use will be recorded to minimize variability. Moreover, all outcome assessors will remain blinded to treatment allocation throughout the study to reduce measurement bias. The same assessor will evaluate a given participant across study visits to reduce inter-rater variability. All assessors will receive standardized training prior to study initiation. The 6MWT will be performed 1–2 h after routine medication administration to minimize variability. Duplicate tests will not be performed unless clinically indicated.

The secondary outcomes will include: (1) major adverse cardiovascular events (MACE, including cardiac death, non-fatal myocardial infarction, and rehospitalization due to HF) at 3 and 6 months. All major adverse cardiovascular events and heart failure-related rehospitalizations will be reviewed and adjudicated by an independent committee blinded to treatment allocation; (2) BNP levels at week 24 compared with baseline; (3) NYHA class functional classification at week 24 compared with baseline; (4) quality of life score of the Kansas City Cardiomyopathy Questionnaire at week 24 compared with baseline.

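### The only visit labelled 'Baseline' falls about 6 days into treatment, and the protocol never says whether the primary analysis uses that 6MWT or the pre-treatment one from Screening

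*Protocol article*

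**What the plan says.** All references are to the protocol article.

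- **Section 2.8, text.** Before treatment: "The study will start with a 7-day preliminary phase where eligible individuals will provide their consent and initial information will be gathered". Then: "Future appointments will be planned for 6 days ± 1 day (visit 1"), in a sentence that ends "12 weeks ± 3 days (visit 3) after starting the treatment". Visit 1 is therefore 6 ± 1 days after treatment starts.
- **Section 2.8, Table 1.** The column with that timing is headed "Baseline (6D ± 1d") and sits under the treatment period. Allocation and the first drug distribution are marked in the preceding Screening column (−7D-0D). The row "Confirmation of medication compliance" has its first mark in the day-6 column. The 6MWT, BNP, NYHA class and KCCQ are marked at both Screening and day 6.
- **Section 2.9.** "The primary outcome of the trial will be the variation in the 6-minute walk test by week 24 as compared to baseline". BNP, NYHA class and KCCQ at week 24 are likewise compared with baseline.
- **Section 2.15.** The primary analysis is "analysis of covariance (ANCOVA) with baseline values and key covariates (age, sex) as covariates to adjust for potential confounding". The imputation model for missing 6MWT data also takes the baseline 6MWT as a predictor.

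No section states which of the two early measurements is the baseline.

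**The concern.** A baseline used for a change score or as an ANCOVA covariate should be measured before treatment can affect it. Here the only visit that carries the name is on treatment. A programmer who follows Table 1 literally would take the day-6 6MWT both as the value subtracted and as the covariate. Any effect of the granules in the first six days would then be taken out of the week-24 comparison.

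The protocol's own rationale does not exclude an early effect: the Introduction and Discussion describe action on fluid retention, less diuretic use and more urine output. Two readings of the primary endpoint are open, and the protocol as written does not settle which one applies.

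**Working it through.** **1. Is the day-6 visit really on treatment?** Four features of section 2.8 agree. The text counts visit 1 from the start of treatment. Table 1 gives the same 6 ± 1 days and places the column in the treatment period. Allocation and first drug distribution come earlier, at Screening. Compliance is checked at day 6, which presupposes dosing. Text and table agree on the timing, so the timing does not look like a misprint; the name of the column is the part in doubt.

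**2. The plan's own figure.** Inputs from section 2.14: difference 50 m, SD 72 m, two-sided α = 0.05, power 90%, dropout 10%.
- Two-sample t-test: 44.56 per group, rounded up to 45. Power at 45 per group is 90.3%.
- Dropout: 45 / 0.90 = 50 per group, 100 in total.

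The stated sample size reproduces and is not in question here.

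**3. What ANCOVA estimates with each baseline.** Let X be the covariate, b its within-group slope, and δ24 and δ6 the true treatment differences at week 24 and day 6.

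Estimate = (difference in week-24 means) − b × (difference in mean X)

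- X from Screening: the expected difference in X is 0 by randomisation, so the estimate targets δ24.
- X from day 6: the expected difference in X is δ6, so the estimate targets δ24 − b·δ6.

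Using the change from X as the outcome gives the same answer: the outcome difference becomes δ24 − δ6, the slope becomes b − 1, and (δ24 − δ6) − (b − 1)·δ6 = δ24 − b·δ6.

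**4. Illustration.** δ24 = 50 m is the planning value in section 2.14. The protocol gives neither δ6 nor b; both are assumed.

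| Assumed δ6 | b = 0.5 | b = 0.7 | b = 0.8 |
|---|---|---|---|
| 0 m | 50 m | 50 m | 50 m |
| 5 m | 47.5 m | 46.5 m | 46 m |
| 10 m | 45 m | 43 m | 42 m |
| 15 m | 42.5 m | 39.5 m | 38 m |

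Example: 50 − 0.8 × 15 = 38 m.

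**5. Why no single power figure follows.** Section 2.14 does not say whether 72 m is the SD of the 6MWT itself or of its change. With b = 0.8 and equal variances at the two visits, the correlation is 0.8 and the ANCOVA residual SD is √(1 − 0.8²) = 0.6 times the raw SD.
- 72 m as raw SD: residual SD = 72 × 0.6 = 43.2 m.
- 72 m as change SD: raw SD = 72 / √(2 × (1 − 0.8)) = 113.8 m; residual SD = 113.8 × 0.6 = 68.3 m.

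Power at 45 per group, two-sided 0.05:

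| Estimated effect | Residual SD 43.2 m | Residual SD 68.3 m |
|---|---|---|
| 50 m | >99.9% | 93% |
| 46 m | 99.9% | 88% |
| 42 m | 99.5% | 82% |
| 38 m | 98.5% | 74% |

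The attenuation is the same in both columns, but the loss of power is negligible in one and appreciable in the other.

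**The case against.** The strongest reply is that Screening is the intended baseline and the column is simply misnamed. Initial information is gathered in the lead-in. Echocardiography, myocardial enzymes, inflammatory markers, biochemical indexes and ECG are marked at Screening and not at day 6, so for those measures Screening is the only possible baseline. Section 2.10 places laboratory safety tests at visits 1, 3 and 4, whereas Table 1 has biochemical indexes at Screening, week 12 and week 24, so the visit numbering itself is unsettled. This stands as evidence of intent. It does not remove the ambiguity for the 6MWT, BNP, NYHA class and KCCQ, which are measured at both visits.

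A reader might infer three stronger things that the document does not support.
- **That the primary result is biased.** No section assigns the day-6 value to the analysis, and no day-6 effect is given. Attenuation needs both the literal reading and an effect on walking distance within six days.
- **That the ANCOVA loses the validity it gets from randomisation.** If the drug has no effect at any time, the day-6 value is unaffected and the 5% error rate holds. What changes is the quantity estimated when the drug does act early.
- **That power falls to a particular figure.** Combining a slope of 0.8 with an unreduced SD of 72 m would be inconsistent, as step 5 of the working shows.

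Diuretic usage has no Screening mark, so its first scheduled value is on treatment. This is minor: the outcome is exploratory and section 2.9 rules out confirmatory use.

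**Conclusion.** The protocol is wrong as written on this point. It gives the name 'Baseline' to a visit about six days into treatment and bases the primary outcome, its covariate, the imputation predictor and the change-from-baseline secondary outcomes on that word without further definition. This goes beyond detail left to an analysis plan, because an analysis plan that used Screening would have to depart from the label in Table 1.

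The size is conditional. Under the literal reading, with assumed b = 0.8 and δ6 of 5 to 15 m, a 50 m effect would be estimated 4 to 12 m too low. Section 2.14 treats about 30 m as clinically meaningful, so the upper end of that range is not trivial. If Screening is used, or if the drug does not affect the 6MWT by day 6, nothing is lost. The labelling conflict is certain; the attenuation is only possible.

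**What to change.** - In sections 2.9 and 2.15, define baseline for the primary outcome, all change-from-baseline outcomes, the ANCOVA covariate and the imputation model as the last value before the first dose, taken at the Screening visit.
- In Table 1, rename the 6D ± 1d column 'Day 6 (Visit 1)' and treat its values as post-baseline. Reconcile the visit numbers in section 2.10 with the table at the same time.
- As a minor point, add a Screening mark for diuretic usage.

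The cost is wording and one relabelled column. The pre-treatment 6MWT, BNP, NYHA class and KCCQ are already scheduled, so these outcomes need no new visit or measurement and the sample size is unchanged. The definition should be fixed before anyone sees outcome data by treatment group.
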